### Number of subjects required

With a recurrence rate estimated at 45% for the general population, in order to observe a 25% reduction in recurrence rate that is attributable to the global secondary prevention program, 310 participants per group (a total of 620 participants) are required to achieve at 80% power with Type 1 error rate of 5%.

A 5% increase in the number of participants is planned in order to take into account those lost to follow-up who do not attend all appointments, as well as any early dropouts. The total number of subjects is therefore set at 650.

These 650 professionals were recruited from within ten occupational health services belonging to the participating hospital facilities.

### Descriptive analysis

Baseline characteristics (socio-demographic, socio-professional and history of the disease) will be summarized and compared in the 2 study groups with the use of chi-square tests for categorical variables and two-sample t-tests or Wilcoxon’s test, where appropriate, for continuous variables, to ensure that participants in both groups were similar at the entry of study.

### Analysis of the primary outcome

The percentage of patients with at least one recurrent episode of low back pain during the 2-year follow-up will be compared between the 2 study groups using a chi-squared test. The prognostic factors and the possible interactions between covariables will be tested with the use of Mantel-Haenszel chi-squared analysis. A multivariate logistic regression analysis will be performed to evaluate the effectiveness of the global program after controlling for potential confounding variables.

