### Randomization

Following the inclusion visit, the study group of the participants was decided by random allocation. The randomization was stratified and balanced by blocks between the participating occupational health services. The randomization lists were computed using SAS® statistical analysis software (Version 9.1, SAS Institute Inc., Cary, NC).

Each participant was informed by mail of his assignment to a study group following an entry checkup performed by a physiotherapist. In this letter, the study group was identified and, where appropriate, the timetable for the five global prevention program sessions was included. In order to ensure the objectivity of the evaluations, the occupational health physicians were not informed as to which study group each participant was assigned (single blind). At the time of enrollment, participants were also asked not to reveal their study group to the occupational health physician.

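### Randomization is stratified by occupational health service but the primary chi-squared test is not (valid, slightly conservative); separately, Mantel-Haenszel is named to test interactions, which it cannot do.

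*Protocol article*

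**What the plan says.** **Design.** The Randomization section states: "The randomization was stratified and balanced by blocks between the participating occupational health services". The section on the number of subjects gives the number of strata: "These 650 professionals were recruited from within ten occupational health services belonging to the participating hospital facilities".

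**Primary test.** Under Analysis of the primary outcome, the percentages with a recurrence "during the 2-year follow-up will be compared between the 2 study groups using a chi-squared test". No stratification is mentioned.

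**Mantel-Haenszel.** The next sentence reads: "The prognostic factors and the possible interactions between covariables will be tested with the use of Mantel-Haenszel chi-squared analysis".

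**Adjusted model.** The section ends: "A multivariate logistic regression analysis will be performed to evaluate the effectiveness of the global program after controlling for potential confounding variables". The covariates are not listed.

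**The concern.** There are two separate points.

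**Strata left out of the primary test.** Blocking within services removes between-service variation from the difference between arms. The ordinary chi-squared test still counts that variation in its standard error, so the test is a little too cautious and gives up precision that the design has secured. Some variation between services is plausible. Under Outcomes, the occupational health physician of each workplace learns from the participant why a sick leave was taken, so a leave is classed as a recurrence service by service.

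**A statistic given the wrong task.** The Mantel-Haenszel chi-squared asks whether there is an association after stratification, pooled over strata. Interaction asks whether the association differs between strata. Followed literally, the plan could overlook a complete reversal of effect, or report an interaction where every stratum shows the same effect. What is at stake is the search for factors related to recurrence, a secondary objective. The main comparison of the program with usual treatment is not affected.

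**Working it through.** **1. The plan's own sample size.** The inputs are a control rate given as "With a recurrence rate estimated at 45% for the general population" and an effect given as "in order to observe a 25% reduction in recurrence rate that is attributable to the global secondary prevention program", with a two-sided 5% level and 80% power. Read as a relative reduction, the comparison is 45% against 0.75 × 45% = 33.75%.

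- The two-proportion formula gives 295 per group without continuity correction and 313 with it. Rounding the second rate to 34% gives 309 without correction.
- The stated 310 is therefore reproduced closely as an unstratified calculation. An absolute reduction to 20% would need only 54 to 62 per group, so the relative reading is the right one.
- 620 × 1.05 = 651, in line with the stated 650.

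**2. True level of the unstratified test.** Assumption: service rates have an SD of 0.05 to 0.10 around 0.45. The share of outcome variance lying between services is s = SD² / (0.45 × 0.55).

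- SD 0.05: s = 0.0025 / 0.2475 = 1.0%
- SD 0.10: s = 0.0100 / 0.2475 = 4.0%

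With balance inside services, the true variance of the difference is about (1 − s) times the variance that the chi-squared test uses. The true level is 2 × [1 − Φ(1.96 / √(1 − s))], which is 4.9% and 4.5%.

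**3. Power at 310 per group.** The unpooled SE is √[(0.45 × 0.55 + 0.3375 × 0.6625) / 310] = 0.0390, and 0.1125 / 0.0390 = 2.886. The variance reduction has to be applied to both tests:

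- unstratified: Φ[(2.886 − 1.96) / √(1 − s)]
- stratified: Φ[2.886 / √(1 − s) − 1.96]

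| Service SD | Unstratified | Stratified | Gain (points) |
|---|---|---|---|
| 0.05 | 82.4% | 82.7% | 0.26 |
| 0.10 | 82.8% | 83.8% | 1.02 |

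**4. Check by simulation.** There were 40,000 runs per scenario, assuming ten equal services with 31 per arm in each. Heterogeneity is set on the logit scale. A logit SD of about 0.2 to 0.4 corresponds to the range above (0.05 / 0.2475 and 0.10 / 0.2475).

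| Logit SD | Service control risks | Level, unstratified / stratified | Power, unstratified / stratified |
|---|---|---|---|
| 0 | 45% | 4.6% / 4.6% | 82.3% / 82.3% |
| 0.25 | 35–55% | 4.6% / 4.8% | 82.3% / 82.6% |
| 0.5 | 26–65% | 4.2% / 5.0% | 82.7% / 83.5% |
| 0.75 | 19–73% | 3.7% / 5.0% | 83.7% / 85.9% |
| 1.0 | 13–80% | 3.0% / 5.0% | 84.0% / 87.8% |

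The 4.6% in the first row is the same for both tests, so it is not a cost of ignoring strata. The power gap stays below one point up to a logit SD of 0.5. It reaches two to four points only when service risks differ very widely.

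**5. Mantel-Haenszel and interaction.** These are constructed examples, with two strata of 155 per group.

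- *Opposite effects:* 90/155 against 50/155, then 50/155 against 90/155. The expected count is 70 in each stratum, so the deviations are +20 and −20 and sum to 0. Mantel-Haenszel chi-squared = 0, p = 1.0. For homogeneity (Woolf), each log odds ratio is ±ln[(90 × 105) / (65 × 50)] = ±1.067, with variance 1/90 + 1/65 + 1/50 + 1/105 = 0.0560. The statistic is 2 × 1.067² / 0.0560 ≈ 40.7 on 1 df, p < 0.0001.
- *Identical effects:* 75/155 against 55/155 in both. The deviations are +10 and +10, and the variance is 18.93 per stratum. Mantel-Haenszel chi-squared = 20² / 37.86 = 10.56, p = 0.001. The homogeneity statistic is 0.

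The statistic is silent where interaction is complete and significant where there is none.

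**The case against.** **On the primary test.** An unstratified chi-squared test after stratified randomization is legitimate. Its error is on the safe side, the loss is small, and the service SDs are assumed. All of this stands. A reader might infer that the type I error is inflated or that the trial falls short of its planned power. The level is at or below 5%, and power exceeds 80% in every scenario examined.

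**On adjustment.** The logistic and Cox models could include service, and a condensed article may leave the covariate list to a fuller document. This also stands, so the absence of service from those models is not held against the plan. It does not answer the primary test, which the article fixes without strata.

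**On Mantel-Haenszel.** The sentence also covers prognostic factors, for which the method is suitable, and the authors may have meant a stratified analysis that includes a homogeneity test. The first part stands. The second is possible, but it is not what the text says: "the possible interactions between covariables will be tested with the use of Mantel-Haenszel chi-squared analysis". A reader might also infer that the plan would misjudge how the program's effect varies between subgroups. The article speaks only of interactions between covariables and specifies no such analysis.

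**On effect measures.** One might add that no effect estimate is planned, or that the logistic odds ratio overstates the planned 25% reduction. The Analysis section promises 95% confidence intervals for results, and the outcome is a percentage in each group. For 45% against 33.75% the odds ratio is (0.3375 / 0.6625) / (0.45 / 0.55) = 0.62 beside a risk ratio of 0.75. Which of the two to report from a supporting model is a matter of preference, not an error.

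**Conclusion.** Both points hold, with different weight.

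The mismatch between stratified randomization and an unstratified primary test is real but minor. For service SDs of 5 to 10 points, the calculation puts the cost at half a percentage point of level or less and about one point of power at most. Only heterogeneity well beyond that range would make it matter more, and the documents give no service rates to judge by. Stratifying is a free improvement and does not rescue a flawed test.

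The interaction method is wrong as written, and this conclusion needs no assumption about service rates. Its reach is limited to an auxiliary analysis, and the trial's main conclusion does not depend on it.

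**What to change.** - Make the primary comparison the Cochran-Mantel-Haenszel test stratified by occupational health service, and report the matching stratified risk difference or risk ratio with its 95% CI.
- Keep Mantel-Haenszel for the association of prognostic factors with recurrence. Test interactions with the Breslow-Day homogeneity test or with product terms in the logistic model already planned.

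The cost is a change of wording. Each participant's service is known because it is the randomization stratum, so no new data are needed and the sample size does not rise. The change should be recorded before outcomes are compared by group, so that the choice of test cannot depend on the results.

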#### Secondary objectives

The secondary objectives are: to evaluate the effectiveness of a global secondary prevention program for acute or sub-acute low back pain on the average time to recurrence of low back pain, and in decreasing the chronification of low back pain among professionals working in health care facilities; to identify risk factors for recurrence of low back pain (personal factors, psychosocial factors, sagittal spinopelvic balance); and, finally, to evaluate the feasibility of the global secondary back pain prevention program *via* the assessment of patient compliance to the program, the assessment of the program by the patients, and the evaluation of the operational model of the program by the patients and the health care professionals involved (physiotherapists and occupational health physicians).

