### Implementation of the study

#### Baseline assessment

Baseline data (administrative, socio-demographic and socio-professional data, as well as information regarding the history of their condition) are collected by the occupational health physicians.

After his inclusion in the study, each participant, regardless of group, underwent an individual assessment with a physiotherapist from Centre Médico-Chirurgical et de Réadaptation des Massues – Croix Rouge Française, as well as an X-ray assessment of the spinal column. The clinical characteristics of the participants in terms of deficiencies, disability and handicap were collected during the initial assessment with the physiotherapist using clinical examination and self-administered questionnaires. The lumbopelvic morphotype of each participant was determined using the X-ray assessment of the entire spinal column carried out in the Radiology Department of the Hôpital Femme-Mère-Enfant (Groupement Hospitalier Est, Hospices Civils de Lyon).

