#### Other parameters

##### Evaluation of deficiencies

Information relative to impairments is collected by the physiotherapist at the baseline and the 18-month follow-up visits.

Nature of the evaluation of impairments

1. Pain assessed using the short-form Saint-Antoine pain questionnaire
[4] (QDSA)

2. Intensity of lumbar and radicular pains using a visual analog scale (in mm) between 0 (no pain) and 100 (pain of highest intensity)

3. Lumbar flexibility using the Schöber-MacRae test
[5]

4. Greater and lesser pelvic flexibility using finger-ground distance

5. Hamstring flexibility using the thigh-to-leg angle (with coxofemoral joint at 90°)

6. Rectus femoris flexibility using the heel-to-buttock distance in prone position

7. Abdominal endurance (Shirado test)
[6]

8. Lumbar extensor endurance (Sorensen test)
[7,8]

9. Gluteal endurance (gluteals test)

10. Quadriceps endurance (Killy test)

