### Analysis of the secondary outcomes

The effectiveness of the global program on the average time to recurrence of low back pain will be tested with the use of the Kaplan-Meier method and the logrank test. A multivariate Cox regression analysis will also be performed to adjust for the global program and all potential confounding variables.

The percentage of participants whose low back pain has become chronic in the two years following the program will be compared between the 2 study groups using a chi-squared test.

Qualitative thematic analysis of the content of the perceptions of the program users and of the health care professionals providing the program in terms of its organizational arrangements

This will be a qualitative thematic analysis of the content that aims to identify the elements of satisfaction or dissatisfaction and the degree of acceptability of the program for the various protagonists. These elements will be coded using the categories used initially in the interview guides (deductive approach). New coding categories will be generated through an inductive approach for the topics that do not correspond to the categories laid out in the interview guides. The coding will be carried out using Atlas.ti v5.2 qualitative analysis software
[21].

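### Mantel-Haenszel chi-squared is the only method named for testing prognostic factors, although many are numeric scores; the regression models already planned suit the risk-factor objective better

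*Protocol article*

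**What the plan says.** One secondary objective is "to identify risk factors for recurrence of low back pain", with personal factors, psychosocial factors and sagittal spinopelvic balance given as the groups of interest (Secondary objectives). The Benefits section counts finding such factors among the study's four main advantages, and the Discussion presents the sagittal balance work as an original part of the study.

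The method appears under Analysis of the primary outcome: "The prognostic factors and the possible interactions between covariables will be tested with the use of Mantel-Haenszel chi-squared analysis". The sentence after it gives logistic regression another purpose: "A multivariate logistic regression analysis will be performed to evaluate the effectiveness of the global program after controlling for potential confounding variables". For time to recurrence, Analysis of the secondary outcomes adds: "A multivariate Cox regression analysis will also be performed to adjust for the global program and all potential confounding variables". The general Analysis section promises 95% confidence intervals with the results.

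The candidate measurements are of two kinds.

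- Numeric or scored: pain on a 0 to 100 mm scale, distances, an angle and endurance tests (Evaluation of deficiencies); the Quebec scale (Assessment of functional disabilities); 0 to 10 ratings and the HAD, FABQ and CSQ-F scores (Assessment of handicap and functional impact); the SF-12 (Assessment of quality of life); and sagittal balance measures taken from the X-rays.
- Wholly or partly categorical: the administrative, socio-demographic, occupational and history data, and the spinal type, for which Baseline assessment says "The lumbopelvic morphotype of each participant was determined using the X-ray assessment of the entire spinal column".

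**The concern.** The article does not leave this choice open. It names a test for prognostic factors and gives the regression models other tasks. The named test comes from the analysis of contingency tables, while many of the factors, and most of the psychosocial ones, are scores. Three things follow.

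1. In table form a score has to be cut, which discards information, and the result can depend on where the cut falls.
2. Adjustment works by stratifying. The adjusters must be categories, confounding can remain within a category, and strata thin out quickly as factors are added.
3. The form of the test that avoids cutting gives a p-value but no effect size.

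At stake is the risk-factor objective: a real gradient may be missed, or a factor may be reported without a usable estimate of its strength. Whether the test is suitable for interactions is a separate question and is not taken up here.

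**Working it through.** **Inputs.** From Number of subjects required: 620 participants (310 per group), 45% recurrence, a 25% reduction (read as relative, giving 33.75%), 80% power, 5% type 1 error, ten occupational health services. From Analysis: two-sided tests. The article gives no coding of the factors and no figure for the risk-factor analysis. Normal covariates and the odds ratio per standard deviation below are therefore assumptions.

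**The plan's own figure.** n per group = [1.960·√(2·0.39375·0.60625) + 0.842·√(0.45·0.55 + 0.3375·0.6625)]² / 0.1125² = 295, or 313 with continuity correction. The stated 310 is within 1% of the corrected value. The issue here does not touch it. 620 serves below as the analysed number and 39.4%, the mean of the two rates, as the overall recurrence rate.

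**Information kept when a factor is cut.** Near the null, relative efficiency is the squared correlation between the factor and its coded version. For a standard normal factor cut once at c it is φ(c)² / [Φ(c)(1 − Φ(c))].

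- Median: 0.3989² / 0.25 = 0.637 = 2/π, a loss of 36.3%. In effect 620 × 0.637 ≈ 395 participants.
- 75th percentile: 0.3178² / 0.1875 = 0.539, a loss of 46.1%.
- 90th percentile: 0.1755² / 0.09 = 0.342, a loss of 65.8%.
- Tertiles scored −1, 0, 1: (2 × 0.3636)² / (2/3) = 0.793, a loss of 20.7%. In effect 620 × 0.793 ≈ 492 participants.
- Quartiles and quintiles with equally spaced scores: losses of 14.4% and 11.2%.

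Shape matters too: a median split loses 25% for a uniform covariate and 52% for an exponential one.

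**Uncut scores.** The one-degree-of-freedom Mantel-Haenszel correlation statistic is (n − 1)r², which needs no cut. In one simulated data set of 620 it was 2.99, against a logistic likelihood-ratio statistic of 3.01 and a Wald statistic of 2.98. The loss is essentially nil.

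**Power.** Simulation of the Mantel-Haenszel correlation statistic stratified by arm, 620 participants, 39.4% recurrence, 3,000 runs per effect:

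| Assumed odds ratio per SD | Uncut | Median split | Tertiles | Quartiles |
|---|---|---|---|---|
| 1.20 | 59% | 40% | 50% | 52% |
| 1.26 | 80% | 61% | 71% | 74% |
| 1.30 | 89% | 72% | 81% | 84% |

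**Adjustment by strata.** Ten services × two arms = 20 strata, on average 620/20 = 31 people. Three more binary adjusters give 20 × 2³ = 160 strata, on average 620/160 ≈ 3.9 people and 0.394 × 620/160 ≈ 1.5 recurrences. The test remains valid with strata this small, but a stratum in which everyone or no one recurs, or in which the factor does not vary, contributes nothing.

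**Estimates.** The correlation form returns a statistic and a p-value. The Mantel-Haenszel odds ratio, which does come with an interval, is built from 2×2 tables and so needs a two-level contrast. Neither form gives an odds ratio per unit of a score with the interval that the Analysis section promises.

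**The case against.** The strongest reply is that the article mentions no dichotomy, category or cut-point, and that the correlation form of the test handles numeric scores at no real cost. This stands, and it rules out saying that the factors have to be cut. It does not answer the need for categorical adjusters or the lack of an effect estimate.

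A second reply is that coding of covariates is normally left to the analysis plan. That also stands: missing cut-points are no fault of an article. The point rests on the test that the article does name and on the different task it gives to logistic regression.

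Third, the Cox wording about adjusting for the programme can be read as estimating the other factors, and nothing says covariates enter either model in categories. The models could therefore do this work. The text does not assign it to them, so the reply supports the fix more than it removes the point.

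Fourth, a reader might infer that nearly all candidates are continuous. The documents do not support that. Personal, occupational and history data are partly categorical, the Background names previous low back pain as the main risk factor, and spinal type may be analysed as a class. Several of the numeric measures are listed under Other parameters and are not named individually in the risk-factor objective.

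**Conclusion.** The point holds in a limited form. For the risk-factor objective the article names a method that fits its many scored factors poorly: it either categorises them or tests them without an estimate, and it can adjust for only a few categorical variables at once.

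A reader might go on to infer that the objective as a whole loses about a third of its information. That is not supported. The 36% figure belongs to a median split of a normal covariate and is neither a bound nor a stated plan. Depending on an unstated coding and on the covariate's distribution, the loss runs from about 0% to over 60%. It would affect only the factors that are categorised, and only the Mantel-Haenszel step. The power figures rest on assumed odds ratios and normal covariates and are illustrative.

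The primary comparison, the sample size and the adjusted programme effect are unaffected. This is a secondary-objective matter, worth changing because the better analysis is already within reach.

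**What to change.** State under Analysis that, for the risk-factor objective, prognostic factors are estimated in the planned logistic model (any recurrence) and Cox model (time to recurrence):

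- numeric factors enter on their measured scale, with a check for non-linearity such as a spline term;
- study group and occupational health service are in the model, the latter because randomization was stratified by service;
- each factor is reported as an odds or hazard ratio, per standard deviation or per clinically meaningful unit if numeric, with its 95% confidence interval;
- Mantel-Haenszel is kept for categorical factors or for descriptive display.

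No new data and no new type of model are needed. The cost is a change of wording and slightly more analysis work.
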